## Abstract

The development of effective interventions for diabetes‐related foot ulcers (DFU) healing is vital. This protocol outlines a pilot trial and qualitative study investigating ESWT in DFU healing. A pilot three arm placebo controlled double‐blinded randomised controlled trial. Participants with a DFU will be randomised to high dose (500 shocks/cm^2^), low dose (100 shocks/cm^2^) or sham ESWT, in addition to standard care. The primary outcome will be deliverability of a definitive trial. Secondary outcomes are ulcer healing, quality‐of‐life and healthcare resource use at 6 months. The target sample size is 90 participants. The study is registered on clinicaltrials.gov, reference: NCT05380544 and has ethical approval (REC reference: 22/WA/0089). The qualitative interview study will recruit participants who complete, drop‐out and decline to participate in the pilot trial, and healthcare professionals who deliver DFU care. Maximum variable sampling will be used to recruit participants. Data will be analysed with an inductive exploratory approach using reflexive thematic analysis. The pilot trial will ensure methods used will address the research question in the definitive trial. The qualitative study will explore how patients and clinicians interact with the trial to understand the pilot trial findings.

Summary
The study was co‐designed with patients and the public.The pilot trial will determine deliverability of a definitive trial of ESWT for DFU healing.The qualitative study will explore reasons for engagement and disengagement from participants with the trial and clinicians' attitudes to DFU research.Results will enable trial processes to be adapted for the definitive trial to ensure the trial answers whether ESWT is clinically and cost effective for DFU healing.A limitation is that this is single centre study in England and results may not translate into other healthcare settings.

## Background

1

Diabetes‐related foot ulcers (DFUs) are common. Currently 537 million people worldwide are living with diabetes, of which 10% have a DFU [1, 2, 3, 4]. DFUs are associated with poor healing and recurrent infections resulting in multiple hospital admissions, lower limb amputations and death [5, 6, 7, 8, 9]. Prolonged healing and the sequalae of DFUs have a devasting impact on patients' quality of life [10, 11, 12]. The burden of DFUs is also felt by healthcare systems. DFU care costs an estimated £1 billion per year in England and between $11 billion and $17 billion in the United States [13, 14].

The development of effective interventions to aid DFU healing is crucial. National and international guidelines recognise the low quality of evidence underpinning many DFU treatments and call for further research [15, 16]. Areas requiring specific attention are the clinical and cost effectiveness of dressings and other topical treatments. Sparse and poor‐quality evidence for DFU treatments is potentially restricting patients access to effective interventions, exposing patients to ineffective practises and wasting healthcare resources.

Extracorporeal shockwave therapy (ESWT) is a non‐invasive and easily tolerated topical adjunct for DFU healing [17]. It is proposed to improve healing through activation of angiogenesis, cellular proliferation and modulation of the local microbiome [18, 19, 20, 21, 22, 23, 24]. There is evolving evidence that ESWT may be a clinically effective treatment to aid DFU healing, however the existing evidence is low quality and the optimal dosing for DFUs is unknown [25].

This protocol describes a pilot three arm randomised controlled trial (RCT) of ESWT for DFU healing and a qualitative study. The aim of the pilot RCT is to test the deliverability of the proposed trial design before expansion to a fully powered RCT. The qualitative study aims to understand factors that influence participants' engagement in the pilot trial and how clinicians' views and prior experiences impact their engagement in DFU research.

## Methods and Analysis

2

The pilot RCT protocol is reported with reference to the Standard Protocol Items: Recommendations for Interventional Trials (SPIRIT) and the Consolidated Standards of Reporting Trials (CONSORT) 2010 statement: extension to randomised pilot and feasibility studies [26, 27](Appendix S1). The qualitative study design is reported with reference to the COnsolidated criteria for REporting Qualitative research (COREQ) checklist [28](Appendix S1). The studies have been designed with input from a dedicated patient and public involvement (PPI) group, who have experience of DFUs.

### Objectives

2.1

The primary objective of the pilot RCT is to determine the deliverability of the proposed definitive trial. The secondary objectives are to explore ulcer‐related outcomes, quality of life and healthcare resource use.

The objective of the qualitative study is to understand why participants engage or disengage with the pilot trial and factors that influence clinician attitudes to DFU research.

### Study Design

2.2

A pilot three arm placebo controlled double‐blinded randomised controlled trial and qualitative study nested in the pilot trial (patients) and parallel to the pilot trial (clinicians).

### Study Setting

2.3

A single centre study based in a tertiary care hospital in the United Kingdom (UK). The pilot trial will be conducted in the outpatient setting. Recruited patients (inpatients, outpatients and community patients) will receive the intervention in an outpatient clinic. The qualitative study will be conducted in a private location chosen by the participant and can include the outpatient clinic, a quiet room on the ward, a research office (clinicians only), the university research space, the patient's home, over the telephone or via a videocall.

### Eligibility Criteria

2.4

Patients with an active DFU below the medial malleolus, present for 4 weeks or longer will be eligible to take part in the pilot trial (Table 1). This includes patients with wounds secondary to surgical debridement and minor amputations and DFU infection, without osteomyelitis. Screening will be performed by the research team in collaboration with the members of the DFU multidisciplinary team (MDT).

**TABLE 1 iwj70176-tbl-0001:** Eligibility criteria.

Inclusion criteria	Exclusion criteria
DFU present for ≥ 4 weeks	Interdigital DFU (as the ESWT paddle does not fit between the digits)
Absolute toe pressure ≥ 50 mmHg or an ankle brachial pressure index ≥ 0.7	Diagnosis of malignancy in the treatment area or disseminated, haematological or lymphatic malignancy (contraindication to ESWT)
Capacity to consent	Pregnancy, trying to conceive or breast feeding (contraindication to ESWT)
Willing to receive any of the trial interventions	Active participants in other wound/DFU related trial
Willing to have their DFU photographed	Osteomyelitis^a^
Willing to comply with the follow up schedule	
	Anticoagulation

Abbreviation: DFU, diabetic foot ulcer.

^a^
Clinical suspicion, receiving treatment or proven (radiological or microbiology sample) osteomyelitis.

Participants who complete, drop‐out or decline trial participation will be eligible to take part in the qualitative study. Clinicians nationally who are a member of the DFU MDT will be eligible to participate.

### Interventions

2.5

The pilot RCT will compare high dose, low dose and sham ESWT. High dose ESWT is 500 shocks/cm^2^ and low dose ESWT is 100 shocks/cm^2^. A minimum of 500 shocks will be administered in the high dose arm and a minimum of 100 shocks will be delivered in the low dose arm. The number of shocks in the active arms is based on the current literature [25].

ESWT will be delivered using a PiezoWave^2^ device (Richard Wolfe, Germany) by a trained researcher. The machine will deliver shockwaves at 0.1 mJ/mm^2^ at 5 Hz and penetrate 5 mm. The DFU will be undressed, cleansed with Prontosan(B Braun, UK) and sharp debrided if required (local standard of care). The DFU will then be covered with a clear film and ultrasound gel applied to the ESWT paddle. Care will be made to ensure there are no air bubbles between the ESWT paddle and film and the ulcer bed.

Sham ESWT will be simulated using a 6 min and 30 s audio‐recording of ESWT. A speaker with the audio‐recording of ESWT will be attached to the top of the ESWT machine. The DFU and ESWT machine will be prepared in the same way as the active arms. Instead of pressing the button to begin delivering shockwaves, the play button on the speaker will be pressed to start the recording. The ESWT paddle will be held onto the ulcer for the duration of the recording. This has been a successful method of blinding in other RCTs of ESWT [29].

High dose, low dose and sham ESWT will be delivered three times over a 7 ± 2 days period. This time interval was chosen to coincide with the standard practice of a dressing change once every 3 days. The treatment will be stopped if the patient is unable to tolerate ESWT.

The decision to investigate the dose of ESWT based on varying the number of shockwaves per cm^2^, as opposed to the frequency of sessions, was on the advice of the PPI group. The PPI group felt longer but fewer sessions of ESWT was more acceptable while the effectiveness of ESWT remains unclear. This is because people with DFUs tend to have many healthcare appointments and increasing the burden of appointments may deter some patients from partaking. In addition, a recent systematic review did not find any differences in healing times between number of ESWT sessions or number of shockwaves delivered [25].

All participants will receive standard care outlined by the NICE and IWGDF guidance [15, 16, 30, 31]. This will include regular dressing changes, sharp debridement, offloading footwear, control of infection and optimisation of blood glucose. Specific aspects of standard care participants receive will be reported. There will be no restrictions on concomitant care or interventions.

### Outcomes

2.6

The primary outcome of the pilot trial is cohesiveness of the trial components. This will be judged by the eligibility ratio (the number of patients eligible/number of patients screened), recruitment ratio (the number of participants recruited/number of eligible patients), adherence to treatment (number of participants who complete three ESWT sessions/number of participants in the trial), adherence to follow‐up (number of participants who attend all follow‐up visits/number of participants in the trial), and percentage of missing data at each follow‐up point and overall.

Secondary outcomes of the pilot RCT include ulcer‐related outcomes (time to healing, proportion of DFU healed and reduction in DFU size), quality of life, adverse events and healthcare resource use.

### Participant Timeline

2.7

The pilot RCT flow chart is illustrated in Figure 1. At the first visit participant eligibility will be confirmed, informed consent taken by the research doctor, and the participant will be randomised. The three trial interventions will be delivered within the subsequent 7 ± 2 days. Face‐to‐face (F2F) follow‐up will take place at 6, 12 and 24‐weeks post randomisation. Remote follow‐up from electronic medical notes at 1 and 10 years post randomisation.

**FIGURE 1 iwj70176-fig-0001:**
[figure not shown]
Participant timeline; ESWT: extracorporeal shockwave therapy.

Participants who complete the F2F follow‐up will be invited to take part in the qualitative study following the 24‐week follow‐up visit. Patients who decline to take part in the trial or drop out of the trial will be invited to take part in the qualitative study at the point of declining/dropping out and be interviewed at the earliest convenient time to them. Clinicians will be interviewed at a time convenient to them.

### Sample Size

2.8

The pilot RCT aims to recruit 90 participants overall. This figure is based on the minimum recommended number of trial participants required to estimate the standard deviation to inform a sample size calculation for a definitive trial [32, 33, 34, 35, 36].

Sample size calculation: 23*3 = 69 minimum number of participants*number of arms.

69*0.3% = 21 30% estimated attrition.

69 + 21 = 90.

The qualitative study sample size is informed by informational power, whereby the more information a sample holds, the smaller the sample needs to be [37, 38]. The aim of this study is narrow and each participant will hold experience relevant to the aim of the study. The researcher undertaking the interviews has experience in DFU, treatments and prior experience of interviewing. The combination of patient and researcher experience is likely to result in more in‐depth data exploration, resulting in fewer participants needed. The qualitative study aims to recruit 36 participants in total split between the following groups:
–Complete the trial: 12–Drop‐out of the trip: 6–Decline trial participation: 6–DFU MDT clinicians: 12

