### Allocation

2.10

Participants will be randomised on a 1:1:1 allocation ratio to sham ESWT, low dose ESWT and high dose ESWT. Participants will be stratified by ulcer size (< 1 and ≥ 1 cm^2^) and ischaemia (ABPI 0.7–0.79 and ≥ 0.8; OR absolute toe pressure 50–59 and ≥ 60 mmHg). These two factors are predictive of healing [39, 40]. Stratified block randomisation with randomly varying block sizes of 3 and 6 will be used. Randomisation will be performed using an online randomised tool hosted at York Randomisation Service, York Trials Unit. The site researcher will enter the participants details into the online tool. The York Trials Unit trial manager, Principal Investigator and the site researcher will then receive an email with the participant's trial arm allocation.

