### Data Monitoring

2.16

Eligibility rates, recruitment rates, treatment adherence, follow‐up adherence and adverse events will be reviewed by the trial management group (TMG) monthly and the trial steering committee (TSC) bi‐annually. The TSC will use Stop/Go criteria to decide whether to continue the pilot trial or pause recruitment and amend trial processes. The Stop/Go criteria [50] are:
–Green (continue): > 60% recruitment, adherence to treatment arm and follow‐up attendance per month.–Amber (continue, review trial processes): 30%–60% recruitment, adherence to treatment arm and follow‐up attendance per month.–Red
○< 30% (Stop, amend trial processes) recruitment, adherence to treatment arm and follow‐up attendance per month.○Serious adverse events related to ESWT (stop, review).

The auditing of the trial processes will take place by independent auditors from the Sponsor's Research, Development and Innovation (RD&I) Department.

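### The 30% attrition allowance is added to 69 rather than divided out, so 90 randomised leaves 63 (21 per arm), below the plan's own minimum of 23 per arm

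*Protocol article*

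**What the plan says.** Section 2.8 of the protocol article gives the target and the whole derivation:

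- The target: "The pilot RCT aims to recruit 90 participants overall".
- Its basis: the "minimum recommended number of trial participants required to estimate the standard deviation to inform a sample size calculation for a definitive trial". No other ground for the size of the trial is given.
- The minimum: "23*3 = 69 minimum number of participants*number of arms".
- The attrition allowance, labelled "30% estimated attrition" and printed in full as "69*0.3% = 21 30% estimated attrition".
- The total is then the sum of 69 and 21, which is 90.

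The Allocation section (2.10) sets a 1:1:1 ratio, so 90 means 30 per arm.

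**The concern.** The minimum is tied to estimating a standard deviation, and only participants who provide outcome data contribute to that estimate. Adding an attrition allowance makes sense only if 69 is the number that must remain after losses. The allowance, however, was worked out as 30% of 69, while the losses will be 30% of those randomised. These are different quantities, and the first is smaller. If the attrition assumption is right, the trial is expected to finish below the only size requirement that it states. A reader of section 2.8 would take 90 to secure 23 per arm at 30% attrition, and it does not. The method also matters beyond the pilot, because the same step applied to a definitive trial would under-recruit there too.

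**Working it through.** **Inputs.** From section 2.8: 23 per arm, 3 arms, 30% attrition, target 90. From section 2.10: 1:1:1 allocation.

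**Step 1: reproduce the plan's figure.**
- Minimum: 23 × 3 = 69.
- Allowance: 69 × 0.30 = 20.7, rounded to 21.
- Total: 69 + 21 = 90. Equivalently, 69 × 1.30 = 89.7, rounded up to 90.

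The stated 90 is reproduced exactly by the additive form n × (1 + d), where d is the attrition proportion. The printed multiplier of 0.3% cannot be meant: 69 × 0.003 = 0.2, not 21.

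**Step 2: what 90 delivers at 30% attrition.**
- Remaining: 90 × (1 − 0.30) = 63, and 63/3 = 21 per arm.
- Shortfall: 69 − 63 = 6 in total (6/69 = 9%), and 23 − 21 = 2 per arm.

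**Step 3: the number that would meet the minimum.**
- n/(1 − d) = 69/0.70 = 98.6, rounded up to 99, or 33 per arm.
- Check: 33 × 0.70 = 23.1 per arm.
- This is 9 more than 90 in total and 3 more per arm.

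**Step 4: the attrition that 90 can absorb.**
- 1 − 69/90 = 21/90 = 23.3%.

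**Step 5: what the shortfall costs in precision.** The 95% confidence limits for a standard deviation are the estimate times √(df/χ²), using the 97.5% and 2.5% points of chi-square. The degrees of freedom are n − 1 for a single arm. For a standard deviation pooled over three arms they are the total minus 3. The formula assumes roughly normal data.

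| Estimate | Lower multiplier | Upper multiplier |
|---|---|---|
| One arm, n = 23 (22 df) | 0.77 | 1.42 |
| One arm, n = 21 (20 df) | 0.77 | 1.44 |
| Pooled, 69 in total (66 df) | 0.855 | 1.205 |
| Pooled, 63 in total (60 df) | 0.849 | 1.217 |

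The article does not say whether the standard deviation will be pooled, so both cases are shown. The difference is small in either.

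**Step 6: how likely 90 is to meet the minimum.** Suppose each participant independently has a 70% chance of being retained. This is an added assumption, used only for illustration. The chance of keeping at least 69 of 90 is then about 10%. The chance of keeping at least 23 of 30 is about 28% in one arm and about 2% in all three arms (0.281³ = 0.022).

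**The case against.** The strongest case on the other side is that the slip hardly matters. Step 5 shows almost no loss of precision. The Statistical Analysis section (2.14) plans no hypothesis test, and the primary outcome is deliverability, which itself includes adherence to follow-up. No primary conclusion depends on 63 rather than 69. All of this stands, and it limits how serious the point is.

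A second objection is that a participant who drops out is not always without data. Ulcer measurements and quality of life are also taken after the third treatment and at 6 and 12 weeks, and routine records are used for those lost to follow-up (Data Collection, 2.12). Someone lost before 24 weeks can therefore contribute to some estimates. This stands in part. Table 2 lists ulcer area and depth as direct measurements only and the quality-of-life questionnaires as patient-reported only, so records would not replace them. Section 2.8 also does not use this argument to lower the 30%.

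A reader might go further and infer that the Stop/Go criteria in Data Monitoring (2.16) repeat the error, because follow-up above 60% is rated Green while 69 of 90 needs 77%. The document does not support this. Those criteria concern "recruitment, adherence to treatment arm and follow‐up attendance per month". They are monthly operational rates, not final retention, and nothing in 2.16 links them to 69 or to the precision of a standard deviation. Amber also calls for a review of trial processes, so low rates do prompt action. A Green line at 77% would rate the trial Amber when follow-up ran exactly at the 70% that the plan's attrition assumption implies. Sections 2.8 and 2.16 do not contradict each other.

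**Conclusion.** The point holds. Section 2.8 applies the attrition allowance to the wrong base, and at the plan's own 30% the target of 90 yields 63, or 21 per arm, rather than 69, or 23 per arm. The conclusion needs only the figures printed in 2.8, equal allocation, and the reading of 69 as the number that must remain after attrition. That reading is the only one under which an attrition allowance makes sense. The derivation is printed in full, so the point does not depend on anything a fuller protocol or an analysis plan might add.

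It is a should-fix. The stated justification is wrong as written, but the precision of the standard deviation barely changes. The 0.3% is a typographical slip with no numerical consequence, since the correct percentage follows on the same line.

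**What to change.** Keep the target of 90 and restate what it delivers in section 2.8, for example: *Randomising 90 participants gives 69 (23 per arm) if attrition is at most 23%; at the assumed 30% it gives 63 (21 per arm).* Correct 0.3% to 30% in the same line.

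The cost is a wording change in one section and a slightly less favourable stated figure, with no extra participants. If the sponsor prefers to hold 23 per arm at 30% attrition, the target becomes 99 (33 per arm), which is 9 more participants. Given how little precision is lost, restating the figure is enough. The Stop/Go thresholds need no change on this account. The sample size for the definitive trial should divide the attrition allowance out.

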### Recruitment

2.9

All pilot RCT participants will be recruited from one tertiary care hospital from the inpatient and outpatient services, with links to the community diabetic foot services. The National Institute of Health and Social Care Research (NIHR) Clinical Research Network will also support recruitment to the study through their contacts with local general practice and community services (study reference CPMS: 52540). The trial will recruit patients over an 18 months recruitment period.

Potential participants will be approached by the research team after discussion with the clinical team and provided a patient information sheet (PIS). This will be followed by a telephone call within the subsequent 7 days to allow patients time to read and understand the information. If a researcher is not available, the clinician can provide the patient with a PIS and complete a consent to contact form.

A log of all screened patients will be kept to document reasons screened patients were not eligible and eligible patients did not enter the study. This will be used to monitor for under‐representation of under‐served groups and identify barriers to entering the trial.

Qualitative study participants will be recruited from the same patient pool as the pilot RCT participants. Purposeful sampling will be used to recruit participants with varying demographics (gender, age, ethnicity), treatment allocation and wound severity (based on Wound Ischaemia, foot Infection stage). Patients will either be approached at a F2F appointment or invited via the telephone. Clinicians will be recruited nationally using purposeful sampling to ensure variation based on the healthcare professional group, location in the United Kingdom and type of healthcare setting. They will be identified at national conferences, through the Vascular Society Diabetic Foot Specialist Interest Group, X (formally Twitter) and snowballing. Clinicians will be approached in person or via email. All potential participants will be provided with a PIS. A log will be kept of all screened patients and clinicians to record reasons they were ineligible or declined participation.

### Allocation

2.10

Participants will be randomised on a 1:1:1 allocation ratio to sham ESWT, low dose ESWT and high dose ESWT. Participants will be stratified by ulcer size (< 1 and ≥ 1 cm^2^) and ischaemia (ABPI 0.7–0.79 and ≥ 0.8; OR absolute toe pressure 50–59 and ≥ 60 mmHg). These two factors are predictive of healing [39, 40]. Stratified block randomisation with randomly varying block sizes of 3 and 6 will be used. Randomisation will be performed using an online randomised tool hosted at York Randomisation Service, York Trials Unit. The site researcher will enter the participants details into the online tool. The York Trials Unit trial manager, Principal Investigator and the site researcher will then receive an email with the participant's trial arm allocation.

